
## 4.2 SCIENTIFIC RATIONALE FOR STUDY DESIGN

**Rationale for site selection:** The overall goal of this project is to improve the care of children in rural and underserved populations with ADHD. We are using strategies that have been proven successful in urban areas and refining and testing these in rural areas. There is a documented need to address the deficit in care caused by geographic distance and variability in electronic medical records (EMRs) across rural environments. In order to successfully implement the intervention while still targeting a rural population, we will seek large rural practices (caring for >700 children in the study inclusion age group) in small cities (<50,000 people) that experience shortages of pediatric sub-specialists (e.g., developmental-behavioral pediatricians) and mental health providers due to geographic barriers (>30 minutes travel distance from a pediatric academic medical center). With 700 children and a pediatric ADHD prevalence of 11%, we would expect on average 77 children with ADHD across the inclusion age group. Many will be initiating stimulant medication for the first time considering median age of onset is 6 years. A driving distance of 30 minutes was used as it is a standard that has been proposed by health departments and used in prior studies.

**Rationale for caregiver/child dyad selection:** We will select children 5-11 years of age with a diagnosis of ADHD without serious mental health comorbidity, who have not previously been treated with a stimulant medication or have not received stimulant medications for the last 3 months. This includes a new diagnosis of ADHD or a prior diagnosis without stimulant treatment. Children aged 5-11 years are most commonly newly diagnosed with ADHD and the caregiver report of symptoms in this age group is of utmost importance. We seek children with a stimulant-naïve ADHD diagnosis because they need to have medications titrated quickly in order to optimize symptom control and support improved academic and social outcomes. Lastly, we will exclude children with serious mental health or neurodevelopment conditions as their care may be more complicated, necessitating in-person visits.

**Rationale for randomizing at the patient level:** RAMP is an automated communication tool designed to eliminate the work burden for providers of requesting and receiving ADHD symptom data from participants. Thus, providers will not be able to reproduce the RAMP intervention for control participants. However, this is an unblinded pilot, and we do not expect providers to change their patient counseling based on participant condition allocation. Therefore, providers should not be confused by receiving RAMP Reports for some study participants (in the experimental condition) and not receiving RAMP Reports for others (in the control). While providers may increase the frequency of their self-initiated outreach to control participants because of the frequency with which they receive RAMP Reports for experimental condition participants, this bias would likely result in more Type II (false-negative) errors for determining intervention effectiveness, which is preferable to Type I (false-positive) errors.

**Rationale for using digital education handouts:** The digital education handouts will be sent via email to the control group and will serve as an attention control. They will consist of information regarding a general pediatric health topic and will be emailed at intervals matching the RAMP requests in the intervention group.

**Rationale for the schedule of [study assessments](#):** The study team will collect the diagnostic assessment from both the intervention and control groups at 0 months (enrollment), as well as a [study assessment](#) (not shared

with provider and clearly marked as such) at Day 90 (-30/+15) — the study final participant follow-up. The diagnostic assessments will be on paper and will be obtained from the diagnosing provider with caregiver permission. The subsequent [study assessments](#) will be obtained either on paper or electronically (caregiver choice). These [study assessments](#) will serve as markers of retention. Caregiver participant incentives will be based on return of these [study assessments](#).

#### 4.3 END OF STUDY DEFINITION

The end of the study is defined as the date when all study activities for all participants are completed or determined to be out of window as defined in this protocol.

The study will end for caregiver/child participants after they have reached 90 days post enrollment and either completed their final [study assessment](#) or failed to complete it by Day 105.

The study will end for provider participants after they have completed the provider survey linked to their last enrolled patient's 3-month RAMP report, or failed to complete it within the review window.

## 5 STUDY POPULATION

### 5.1 INCLUSION CRITERIA

**Caregiver/child dyad eligibility:** To be eligible to participate in the trial, caregiver/child dyads must attend one of the four participating primary care clinics and meet the following inclusion criteria:

The child must

- be under the care of a participating provider
- be aged 5-11 at enrollment
- have a diagnosis of ADHD
- be initiating stimulant medication for treatment for the first time or have not received stimulant medication for the last 3 months
- be attending in-person elementary school

Primary caregiver must

- be willing and legally able to give consent
- have access to a smartphone
- be English-speaking
- reside with the child at least 3 days per week
- complete an initial symptom assessment prior to starting stimulant treatment and be willing to provide a copy to the study team

Eligible children include those receiving a new ADHD diagnosis, those having a prior diagnosis without stimulant medication treatment, and those having a prior diagnosis but have not received stimulant medication for the last 3 months. Children only receiving adjunct (non-stimulant) medication are ineligible. Only one child per household can enroll. The participating caregiver is defined as the parent or legally authorized representative (LAR) who can consent for their child's medical treatment and should be with the child at least 3 days per week.

**Practice selection:** A total of 4 pediatric or family practice locations will be selected from two ISPCTN awardee sites, with each site recruiting at least 1 practice location for participation. Practices should care for at least 700 patients aged 5-11 years and should regularly diagnose and manage pediatric ADHD. With 700 children and a pediatric ADHD prevalence of 11%, we expect on average 77 children with ADHD across the inclusion age group, many of whom will be initiating stimulant medication for the first time, considering median age of onset is 6 years. Practices will be designated as rural if they are at least 30 minutes travel distance from a pediatric academic medical center (similar to prior studies) and are located in a city with less than 50,000 people. Practices will be designated underserved if at least 40% of its pediatric patient visits are covered by Medicaid. Practices must use an EMR as this pilot aims to use typical practices in preparation of the full-scale trial. 2019 National Electronic Health Records Survey found that 89.9% of office-based physicians were using an EMR.

Use of electronic prescribing is preferred but not required. Practices must also be willing (and preferably experienced) in using the Vanderbilt Assessment as their primary tool for ADHD diagnosis and management. Providers must agree in concept to participate in the ADHD Best Practice education, as well as instruction on using the RAMP platform and will provide informed consent (see provider eligibility below). Interested ISPCTN sites will assess eligible practices and choose the best fit. Locations will be submitted by interested ISPCTN sites and will be evaluated by the Data Coordinating Operations Center (DCOC). Selection will occur and ISPCTN sites will be notified.

**Provider eligibility:** Providers of the eligible practices will be included if:

- they manage ADHD care in patients age 5-11 years
- provide informed consent
- agree to use the RAMP platform if they care for patients randomized to use it
- agree to provide information to potential participants about the study and contact the research coordinator if interested

ADHD Best Practices education at the start of the project will include titration and monitoring guidelines from the current AAP practice guidelines. In the same training session, providers will be educated about accessing the RAMP Reports, oriented to the potential data provided, and instructed on documenting their review in the platform. Providers will be given workflow instructions to obtain the RAMP Reports from teachers. Participating practices will receive compensation of \$4000 for their time and engagement working on the study. New providers joining a practice who meet these eligibility criteria will be consented and trained as above at the time of onboarding.

## 5.2 EXCLUSION CRITERIA

Participants will be excluded if:

- **Child**
  - has serious mental health comorbidities (Children with depression, anxiety, oppositional defiant disorder will be permitted to participate. Children with schizophrenia, bipolar disorder, conduct disorder and those who have been hospitalized for any mental health condition will be excluded from the study.)
  - has severe neurodevelopment disorders (Children with well-controlled seizure disorders will be permitted to participate.)
  - is currently receiving, or previously received, atypical antipsychotic medication treatment
  - is or becomes pregnant
- **Caregiver**
  - none
- **Provider**
  - none

### 5.3 LIFESTYLE CONSIDERATIONS

Not applicable.

### 5.4 SCREEN FAILURES

The study team will consider the caregiver/child dyads who undergo screening but who do not enroll in the trial to be screen failures, including those who are contacted by the study team but who do not meet inclusion and/or exclusion criteria. Research coordinators must document and retain the reason for screen failure.

### 5.5 STRATEGIES FOR RECRUITMENT AND RETENTION

#### 5.5.1 RECRUITMENT OF POTENTIAL PARTICIPANTS

Research coordinators will work with practice providers to schedule the ADHD Best Practice education, RAMP platform orientation, and informed consent encounters for providers who care for children with ADHD at each practice. ADHD Best Practice education and RAMP platform orientation will introduce providers to the study in a group setting. Providers will have an opportunity to ask questions and sign the consent documents at that time or schedule private consent encounter with a research coordinator.

Providers will notify research coordinators of potential participants following an initial evaluation visit for ADHD. Research coordinators may also search for potential participants in the EMR. A partial HIPAA waiver will be obtained for pre-screening procedures used to identify potential participants. Upon return visit and completion of ADHD diagnosis and initiation of stimulant therapy, caregiver/child dyads will receive a flyer from the provider and, if amenable, be referred to a research coordinator for remote review of the project to assess their interest. Research staff will contact interested caregivers by phone, email and/or text. If caregivers are unreachable by any of these methods at first contact, research staff will follow up with at least two additional outreach attempts by one or more methods (phone, email, and/or text) during the first five weeks after stimulant medication is initiated. After a detailed discussion of the project, if a caregiver does not want to participate, the research coordinator will ask reason for refusal and document this information (no PHI required). For all interested caregivers, the study team member will complete the eligibility screening and alert PI to review the eligibility (if needed). Enrollment procedures will include informed consent, HIPAA and FERPA authorizations, orientation to the platform and enrollment text, and obtaining demographics and baseline medical history. Research coordinators will also ask for the caregiver's permission to obtain the initial diagnostic assessment from the diagnosing clinician. Eligible caregiver/child dyads will be randomized to either intervention or control group (1:1).

To keep all PHI protected, keep recruitment practices uniform and have a balanced perspective of the study during the consent process, research coordinators will be trained in the specifics of the study procedures. Research coordinators will be certified in GCP and trained in obtaining informed consent remotely. The data manager will review all forms as well as what data is allowable to retain with research coordinators. Role play of recruitment, enrollment and informed consent process by study PI or their designee before study begins,

followed by planned observation for first few enrollments and then periodically throughout the study. Additional details regarding recruitment training will be stated in the MOP.

The Study PI, site PI, and coordinators will regularly meet to review enrollment status. Practice site calls with the site champion and ideally at least one provider may occur during the enrollment period to keep practice staff informed about the progress of the study. Individual assistance for a site will be provided if a site has not been able to enroll at least 4 caregiver/child dyads within 6 weeks of initiating recruitment/enrollment.

---

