The entire timeline will span 17 months with three phases. In the first phase of the study, the providers from the participating practices will receive ADHD Best Practices education and training in the portal use, and will be asked to provide informed consent. A member of the clinic staff (nurse, medical assistant or practice manager) will be identified as site champion. The site champion will facilitate communication between the site study team and the clinic staff. The second phase of the study will focus on child/caregiver and provider utilization. Providers will identify patients with a diagnosis of ADHD who are being started on stimulant medication to be contacted by study staff for enrollment. Research coordinators will discuss the study, perform eligibility screening and obtain consent (if deemed eligible by PI). The consented caregiver/child dyads will be randomized to intervention (requests to submit the RAMP Reports for 3 months) or control (usual care with attention control) groups. Families will be approached until 36 caregiver/child dyads are enrolled (only one child in a family may be enrolled). Each practice will have 6 weeks to enroll 9 participants. After the 6 weeks, practices with low enrollment will receive additional supports. Each week, progress to target will be evaluated to determine if any practice needs additional resources. If multiple practices do not meet enrollment goals, the study team may consider relaxing exclusion/widening inclusion criteria (ex. include patients undergoing re-titration, widen age criteria) and/or opening enrollment. Enrollment will be paused for 3 months from the last month of school to the start of the new school year (beginning of May to end of July). This will decrease the burden on practices and study staff during the time of the year with the fewest number of ADHD diagnoses. Once enrolled, caregiver/child participants will be randomized to either the intervention or control group and followed for approximately 3 months. Participants randomized to the intervention group will submit RAMP reports weekly for 4 weeks and then monthly for 2 months. Participants randomized to the control group will receive digital education handouts at the same frequency as the RAMP reports in the intervention arm. Research coordinators will periodically review the child participant's EMR and mark how many paper symptom assessments are returned while enrolled on the study for both groups. Research coordinators will also access the RAMP platform to log RAMP reports returned by caregivers/teachers, RAMP reports reviewed by providers, and provider survey results. All caregiver participants will complete a 90-day Vanderbilt Assessment as a retention measure (see section 1.2.1 for more details). This phase will continue until all 36 participants have completed their 3-month study period. In the third phase, the above endpoints will be calculated, the full-scale trial will be designed, and the findings presented in a manuscript.

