### 9.2 SAMPLE SIZE DETERMINATION

A total sample of 36 participants was agreed in accordance with published guidance for pilot studies. Up to 36 caregiver/child dyads and 20 providers will be enrolled. Our proposed sample size is also consistent with the recommendations of Whitehead and colleagues (2016). Their derived new stepped rules of thumb for a pilot trial sample size vary depending on an estimated standardized effect size for the main efficacy trial; therefore, if we assume a medium Cohen's effect (i.e.,  $0.3 \leq \delta \leq 0.7$ ) and 90% power for the main trial, a sample size of 36 participants with 18 randomized to each intervention arm in the pilot study is sufficient.

With a focus on participant recruitment and adherence, a sample size of 36 allows the study team to estimate an expected recruitment rate of 25% and adherence rate of 50%, each within 12-14 percentage points, with a confidence level of 90%. We expect the rate of return of the RAMP Reports to be a comparable rate to the general survey response rate of 52.7%, though it may be higher as the platform aims to function as an engagement tool.

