#### 9.4.8 TABULATION OF INDIVIDUAL PARTICIPANT DATA

The statistical team will provide a detailed description of participant disposition, will tabulate the number of enrolled participants overall and by study site, and will present this data as counts and proportions. Additionally, the statistical team will summarize the number of participants either completing or discontinuing the study using counts and proportions.

---

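### Section 9.2 justifies 36 dyads partly by the precision of a recruitment rate that has no defined denominator, whose early declines need not be counted, and that no analysis in 9.4 estimates

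*Protocol*

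**What the plan says.** Section 9.2 first rests the sample on pilot-study guidance ("A total sample of 36 participants was agreed in accordance with published guidance for pilot studies") and on a stepped rule of thumb giving 18 per arm. It then adds a precision argument: "With a focus on participant recruitment and adherence, a sample size of 36 allows the study team to estimate" two quantities, namely an "expected recruitment rate of 25% and adherence rate of 50%, each within 12-14 percentage points, with a confidence level of 90"%. Neither rate is given a denominator. Section 4.1 fixes when recruitment stops: "Families will be approached until 36 caregiver/child dyads are enrolled".

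Section 5.5.1 describes how families reach the study team:

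- Providers tell coordinators about potential participants after the initial ADHD evaluation visit.
- Coordinators may also search the EMR, under a partial HIPAA waiver for pre-screening.
- Once the diagnosis is complete and a stimulant is started, "caregiver/child dyads will receive a flyer from the provider and, if amenable, be referred to a research coordinator".
- Coordinators then contact interested caregivers. A reason for refusal is documented after a detailed discussion with the coordinator.

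Section 5.4 defines the screening record: "The study team will consider the caregiver/child dyads who undergo screening but who do not enroll in the trial to be screen failures". The reason for each screen failure must be kept.

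Section 3 lists no recruitment endpoint. Within section 9.4, subsection 9.4.8 promises a description of participant disposition, says the team "will tabulate the number of enrolled participants overall and by study site", and adds counts of those completing or discontinuing.

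**The concern.** A recruitment rate needs a numerator, a denominator and an estimate. The protocol fixes only the numerator, and its precision figure appears to treat that numerator as the denominator.

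The records that the protocol requires start late. A family that declines when handed the flyer, or that is never handed one, need not be counted. If the rate is later formed from the dyads that were referred or contacted, those families drop out of the denominator and uptake looks better than it was among all eligible children.

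The results are meant to inform a full-scale trial. A rate on the wrong base would understate how many eligible children that trial needs at its practices. This cannot be left entirely to the statistical analysis plan, because declines that were never logged cannot be recovered at analysis.

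**Working it through.** **Inputs.** From section 9.2: n = 36, recruitment rate 25%, adherence rate 50%, 90% confidence (z = 1.645), stated precision 12 to 14 points. From section 4.1: 36 is the number enrolled. Not in the protocol, so assumed: the share of eligible families that is referred.

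**Step 1. Reproduce the plan's figure.** Wald half-width = z × √(p(1−p)/n).

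- Recruitment: 1.645 × √(0.25 × 0.75/36) = 0.119, or 11.9 points.
- Adherence: 1.645 × √(0.50 × 0.50/36) = 0.137, or 13.7 points.

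These are the stated 12 and 14 points. The Wilson score interval gives 11.6 and 13.2. The figure reproduces with 36 as the denominator of both rates.

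**Step 2. Check the denominator.** If 36 were the number of families in the recruitment denominator, a 25% rate would give 0.25 × 36 = 9 enrolled dyads. Section 4.1 says recruitment continues until 36 are enrolled, so 36 is the numerator. At 25%, the denominator would be 36/0.25 = 144 families, and the half-width 1.645 × √(0.25 × 0.75/144) = 0.059, or 5.9 points (Wilson interval 19.6% to 31.4%). Allowing for the fact that enrollment stops at a fixed 36 makes no difference to this approximation: 1.645 × 0.25 × √(0.75/36) = 0.059.

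**Step 3. Which families must be recorded.**

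| Stage in 5.5.1 | Count required by the protocol text? |
|---|---|
| Provider notification after initial evaluation | Notification required, but it precedes diagnosis and stimulant start, so it is not a list of eligible children; no reconciliation with later referrals |
| EMR search | Optional; no count required |
| Eligible but not offered a flyer | No |
| Flyer given, family not referred | No |
| Refusal after detailed discussion with coordinator | Yes, with reason |
| Screened, not enrolled (5.4) | Yes, with reason |

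**Step 4. Effect of a late denominator.** Suppose the true uptake among all eligible families is 25% and every enrolling family comes from the referred share s. The rate among referred families is 0.25/s, and the denominator behind 36 enrolled is 36/(0.25/s) = 144 × s.

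| Share referred (assumed) | Rate among referred | Families behind 36 enrolled |
|---|---|---|
| 1.00 | 25% | 144 |
| 0.80 | 31% | 115 |
| 0.65 | 38% | 94 |
| 0.50 | 50% | 72 |

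Reading the right-hand column as the number of eligible families needed would understate the true 144 by 20% (1 − 0.80) to 50% (1 − 0.50) over the range 0.80 to 0.50.

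**Step 5. Is the rate estimated anywhere?** Sections 9.4.1 to 9.4.9 contain no recruitment-rate estimate, and 9.4.1 says the statistical analysis plan will detail the analyses outlined in that section.

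**The case against.** A reader might infer that only families whom the provider judges willing ever come to the study team's notice, and that any recruitment rate from this pilot is therefore inflated and unusable. The protocol does not support that. Section 5.5.1 has coordinators told of potential participants before the flyer and lets them search the EMR, so a fuller denominator is available, though not required. The condition on referral describes the family's own willingness, not the provider's opinion. Inflation follows only if referred or contacted families form the denominator. If the 25% was meant as uptake among those families, a rate on that base is not biased for that quantity.

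Other points on the plan's side also stand. Recruitment precision is one of several bases for 36, and recruitment is not an objective or endpoint. The screening and enrollment figure in section 5.5.2 is not shown, and neither the manual of procedures nor the statistical analysis plan is at hand; any of them may ask for more counts, and the disposition table may include screening data. Accrual time can also be projected from dyads enrolled per practice per month, without a consent proportion.

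A reader might also infer from the amendment summary that slow accrual forced the wider eligibility. The rationale stated there for the version 4 eligibility changes is to increase the number of eligible children; slow accrual is not stated.

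What remains is that the protocol offers this rate as a reason for its sample size without defining it, requiring the data for it or planning its estimate. Notification before diagnosis and an optional search do not fill that gap.

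**Conclusion.** The point holds in a limited form, and the protocol should be changed. Two parts rest on the protocol alone: the recruitment rate used in section 9.2 has no defined denominator and no estimate in 9.4, and its stated 12 points match a calculation on the 36 enrolled dyads. If 25% holds, the right base is about 144 families and the 90% half-width about 6 points, so the error understates the achievable precision and does not weaken the case for 36.

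The third part is conditional. A rate formed among referred or contacted families would exceed uptake among all eligible families by a factor of 1/(share referred). The direction is clear whenever some eligible families are not referred. The size is unknown: 31% to 50% in place of 25% rests on assumed shares of 80% to 50%, and on enrolling families coming only from the referred group. That range illustrates the risk and is not an estimate for this trial.

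**What to change.** - **Section 5.5.1:** make the already permitted EMR search a routine de-identified count, per practice and month of open enrollment, of children meeting the protocol's age, diagnosis and stimulant-start criteria. Log how many were given a flyer, referred, reached, found eligible and consented.
- **Section 9.4:** define recruitment rate = consented / EMR-eligible. Report it with its confidence interval and the proportion passing each stage.
- **Section 9.2:** state that denominator and restate the recruitment precision on it: about 144 families and a half-width of about 6 points at 90% confidence if 25% holds. The adherence figure on 36 needs no change on this account.

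The cost is a small amount of coordinator time each month and one added table. EMR eligibility will be approximate, since criteria such as smartphone access or language may not be recorded, and the reported rate may look less favorable than one based on referred families.
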